A random assignment will be carried out to reduce the threat of selection, and the fact of choosing three conditions is one of the established standards for this type of designs in order to reduce the threat of ambiguous temporal precedence and maturation [38]. Furthermore, the fact that all three conditions involve evaluation periods of 8, 12 and 15 days is due to the established standard of having a minimum of five data points in each phase to reduce the threat of attrition [38]. By choosing at least eight, we make sure to meet it even considering the probability that participants will forget to fill out the assessment one day. Actually, the reason for choosing those days is the temporal stability of the variables that we measured through the study.

In addition, the intervention will begin in a staggered manner with individual sessions (to reduce the threat of the history) and to reduce the threat of testing, a pre-treatment assessment will be performed prior to starting the baseline, to consider that the assessment process itself can have therapeutic effects on participants [38].

The study includes five assessment moments (pre-treatment, baseline, treatment, post-treatment, and follow-up, one every three months until two years after treatment completion). The flow chart of the study design is shown in Figure 1.

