The baseline and psychological intervention will be conducted between the period of acceptance for BS and the BS implementation, that last approximately one year in public health settings. The intervention will be carried out in an online group format through the Cisco Webex platform. The UP will be applied in twelve weekly 2-h online group sessions. To comply with the experimental design of the multiple baseline, when each participant completes the baseline evaluation, they will receive the first online session in individual format (to receive the first session in stages), then they will continue with the second session and the rest of the treatment in group format. The content of each session is shown in Table 2. Participants will receive the therapy support manual [11]. The online group will consist of five to eight participants, one therapist ([name]), and one co-therapist ([name]). For ethical reasons, if any of the patients feel uncomfortable during the study with the online group format, they may leave the group and receive individual onsite attention (treatment as usual). In this case, the content and estimated number of sessions will be the same, although the frequency will be stipulated by the mental health unit depending on its possibilities.

The study plans to conduct a follow-up assessment every three months until two years after treatment completion. All follow-ups will be conducted online. Considering the time interval of the baseline, the psychological intervention and the BS procedure, the two first follow-ups (three and six months after intervention) will be conducted before BS, and the rest will be conducted after BS. In addition, at the baseline and during treatment, the participants must fill out an online survey made up of 14 questions that will ask about the intensity of the emotions of happiness, sadness, anxiety, other emotions, difficulties in emotion regulation, body image, and emotional eating. Through this weekly evaluation, we expect to observe how the participants evolve in the different variables throughout the different treatment modules.

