### 2.5. Measures

The evaluation protocol will be administered online by Qualtrics survey [45] at five different moments: pre-treatment, baseline, treatment, post-treatment, and follow-ups every three months until two years after the intervention. Assessment instruments will include demographic characteristics (age, sex, education, marital status, and employment status), a diagnostic interview, and well-established questionnaires for both primary and secondary outcomes. Next, the primary and secondary outcomes that will be evaluated at the pre, post-treatment, and follow-up periods will be described, and later the specific measures that will be used for the baseline evaluation and during the treatment will be specified. Table 3 shows the distribution of the measures that will be administered during the study.

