### 2.6. Data Analysis

The analyses will be carried out with the statistical package IBM SPSS Statistics version 22.0 for Windows [78]. First, the sociodemographic characteristics of the sample will be analyzed with descriptive statistics, calculating the mean and standard deviation of the scores in the different questionnaires administered. Next, a missing-value analysis and the Little Missing Completely At Random (MCAR) test will be performed to determine whether or not the distribution of missing values is random, and therefore whether the last observation made (LOCF) can be used. Internal consistency will be explored using Cronbach’s alpha.

As the sample size is expected to be less than 50, the normal distribution of the variables will be verified with the Shapiro–Wilk normality test. Depending on the result of this test, parametric or non-parametric repeated measures analysis will be carried out to verify whether or not the differences in the scores of the variables measured at different times are statistically significant. In case the variables follow a normal distribution, parametric repeated measures analysis will be carried out, specifically the Multivariate Analysis of Variance (ANOVA), and in case the variables do not follow a normal distribution, non-parametric repeated measures analysis will be carried out, specifically the Friedman test. If the repeated measures analysis show statistically significant differences between the evaluation time points, post-hoc comparisons will be carried out to correct the level of significance to avoid increasing the type I error. Thus, regarding adjustment for multiple comparisons, the Bonferroni correction will be carried out in case of having performed parametric analysis, and the Wilcoxon signed rank test in case of having performed non-parametric analysis in the comparison of means. More detailed information on this has been added in the data analysis section, explaining step by step which statistical analyzes will be carried out.

Finally, the Reliable Change Index (RCI), which assesses the clinically significant change obtained to determine in which variables the scores have approached those of the normative sample, will be calculated. A clinically significant change will be considered if the RCI score obtained is equal to or greater than 1.96 [79].

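### The non-parametric branch names the Wilcoxon signed rank test as its multiplicity adjustment, but that test adjusts nothing, so type I error across time points is uncontrolled there once any occasion truly differs

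*Protocol article*

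**What the plan says.** Section 2.6 (Data Analysis) lets a Shapiro–Wilk test choose the method: "Depending on the result of this test, parametric or non-parametric repeated measures analysis will be carried out". The parametric route is repeated-measures analysis of variance and the other is the Friedman test. Pairwise testing is conditional on the overall test: "If the repeated measures analysis show statistically significant differences between the evaluation time points", then "post-hoc comparisons will be carried out to correct the level of significance to avoid increasing the type I error". On the adjustment itself, the section states: "the Bonferroni correction will be carried out in case of having performed parametric analysis, and the Wilcoxon signed rank test" in the non-parametric case. It then points to further detail in the data analysis section, which is this same section and holds none.

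On the number of occasions, Section 2.2 says: "The study plans to conduct a follow-up assessment every three months until two years after treatment completion". Section 2.5 refers to "the primary and secondary outcomes that will be evaluated at the pre, post-treatment, and follow-up periods", and Table 3 marks the BDI-II and BAI, for example, at pre-treatment, post-treatment and follow-ups only.

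**The concern.** The sentence puts a test in the place where a correction belongs. Read literally, the parametric branch tests each pair at a reduced threshold and the non-parametric branch tests each pair at the full one. Two outcomes with similar change over time could then be judged differently because of a normality test on roughly 39 people.

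The main exposure is the maintenance question. Hypothesis 2, at the end of the Introduction, says gains will last up to two years. Unadjusted comparisons over many follow-ups can throw up apparent relapse or further gain that is only noise. This is an error in what the article states, not a detail left to a later plan. An analysis plan that repeated the sentence would carry the error with it.

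**Working it through.** **Inputs from the article**
- Full-questionnaire occasions: pre-treatment 1 + post-treatment 1 + quarterly follow-ups over two years (months 3, 6, 9, 12, 15, 18, 21, 24) 8 = 10.
- Analysed sample: 60 × (1 − 0.35) = 39 (Section 2.1). This agrees with the expectation in Section 2.6 of fewer than 50.

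**Assumed, because not stated**
- Alpha 0.05 two-sided for the group tests. The RCI cut-off of 1.96 corresponds to that level. Alpha cancels out of the ratios below.
- Which pairs are compared. The article lists none, so a range is shown.

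The article gives no adjusted threshold or number of comparisons, so there is no stated figure to reproduce.

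**Thresholds.** Pairs among k occasions = k(k − 1)/2. The Bonferroni threshold is 0.05 divided by the number of pairs. Wilcoxon as written stays at 0.05, so the ratio of thresholds equals the number of pairs.

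| Occasions or contrasts compared | Pairs | Bonferroni threshold | Ratio |
|---|---|---|---|
| 3 occasions | 3 | 0.0167 | 3 |
| 4 occasions | 6 | 0.0083 | 6 |
| 6 occasions | 15 | 0.0033 | 15 |
| 10 occasions, pre–post plus pre and post against each follow-up | 1 + 8 + 8 = 17 | 0.0029 | 17 |
| 10 occasions, all pairs | 45 | 0.0011 | 45 |

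**What the Friedman gate does.** Simulated with normal data and no true difference anywhere (10 occasions), at least one unadjusted Wilcoxon test is significant in 0.67 of trials at n = 39 without the gate, and in 0.047 with it. The gate works under the complete null.

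It stops working once one occasion differs. With pre-treatment shifted by one within-person SD (correlation 0.5) and the other nine occasions equal, the gated error among the true nulls is 0.58 at n = 39 and 0.62 at n = 60. With Bonferroni it is 0.02 and 0.03.

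**Sensitivity to the assumptions.** Here n = 39, correlation 0.6, pre-treatment differs by 0.8 SD, and the tests are Friedman followed by unadjusted Wilcoxon. Family-wise error per outcome among the true null pairs:

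| Setting | Error |
|---|---|
| 10 occasions, nine later ones equal, all 36 null pairs | 0.58 |
| 10 occasions, nine later ones equal, post against the 8 follow-ups only | 0.26 |
| As the row above, with an assumed 0.5 SD shift after surgery | 0.10 |
| 4 occasions, later three equal | 0.13 |

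With Bonferroni the error is about 0.03 to 0.04. Repeat runs with other random seeds gave values within about 0.02 of those in the table, and Bonferroni values no higher than 0.04.

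With only three occasions and one of them different, a single null pair remains and the gated error is about 0.05. The inflation therefore appears from four occasions upward.

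**The case against.** The strongest reply is that the omnibus test already guards the post-hoc step, so type I error is not left open. This is partly right. The gate holds the error near 0.05 when nothing changes over time, and it would be wrong to say there is no protection at all. But the study expects a change from pre-treatment, and that change opens the gate.

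A reader might infer a fixed 45-fold difference and a 60% error rate. The article supports neither as a plain fact. Forty-five assumes that every pair is compared. The hypotheses and Table 4 name fewer comparisons of interest (for the RCI), about 17 on this schedule. The 0.6 needs nine equal later occasions, which fits poorly with Section 2.2, where two follow-ups precede surgery and the rest come after it. Nor does the count of ten occasions apply to everything: BMI is also taken at baseline and during treatment, and a MINI diagnosis is not a score for this analysis. The article does not say whether the normality test picks the branch variable by variable or for the whole set.

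It is also fair that this is a pilot whose results the Discussion says must be read with caution. Hypothesis 1 is framed on individual reliable change, and feasibility rests on attendance and satisfaction. That lowers the severity. It does not make the sentence correct, because Table 4 expects significant group differences and the authors themselves chose to control type I error.

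A list of contrasts, or a single primary outcome, is commonly left to an analysis plan, and its absence here is not a fault.

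**Conclusion.** The statement is wrong as written. The non-parametric branch has no multiplicity adjustment, and error across time points is controlled there only if no occasion differs.

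The size depends on what is compared. The thresholds of the two branches differ 3- to 6-fold for three or four occasions and up to 45-fold for all pairs of ten. Family-wise error per non-normal outcome is about 0.1 to 0.6. The error figures rest on assumed correlation, effect size and pattern of later change, and on alpha 0.05; the ratios do not depend on alpha. False follow-up findings are a risk, not a certainty. Should-fix.

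**What to change.** Reword Section 2.6, and carry the wording into the analysis plan, to say that after a significant Friedman test the post-hoc comparisons are pairwise Wilcoxon signed rank tests, with p-values adjusted by Bonferroni (or Holm) under the same rule as the parametric branch. State alpha. Apply the adjustment over the contrasts the hypotheses need: pre against post, and pre and post against each follow-up up to two years (17 on this schedule, so 0.05/17 = 0.0029 under Bonferroni).

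The follow-up contrasts should not be cut to the pre-surgery visits. That would leave hypothesis 2 without group-level post-hoc tests after six months.

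The cost is a sentence or two and no extra data. Fewer results will be nominally significant.

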The multiple baseline design involves the application of the treatment variable in a staggered way over time, through different observational units. This design is suitable for health services research interventions that are focused on changing patient behavior. This methodology facilitates a systematic comparison of pre-intervention and post-intervention measures [35], and conducting a preliminary assessment of a novel intervention [36]. Like randomized controlled trials (RCTs), the multiple baseline design can demonstrate that a significant change in behaviour has occurred and that is result of the intervention. One of the main limitations is that each participant must show changes only when the intervention is applied, and this issue, at a practical level is complicated, can make it difficult for the researcher to draw clear conclusions about the impact of the intervention. In order to reduce this limitation and improve the internal validity, researchers start treatment at different times across settings, behaviors, or people [37]. The multiple baseline design has advantages over the RCTs because this design requires fewer population groups and communities and they may act as their own controls [35]. In this sense, researchers often use this design with several people at once addressing the issue of external validity [37].

In the present investigation, all consecutive patients who are selected to undergo BS and who present anxiety or depressive symptoms or at least one diagnosis of ED, will be asked to participate. Once inclusion criteria are met (see “Inclusion and exclusion criteria” section), each patient will be randomly assigned to one of the multiple baseline conditions: 8, 12, or 15 evaluation days before the intervention. These multiple baseline conditions have been chosen following the current guides for single-case designs [34,38].

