#### 2.5.3. Baseline Assessment

To facilitate the daily baseline assessment, we have summarized in one item the variable we want to evaluate, for example, the emotion regulation strategies. For this purpose, we have chosen the item with the greatest factor load for each variable [73]. Specifically, participants will answer a battery of 19 questions: six questions about the presence and intensity of specific emotions (e.g., happiness, sadness, anxiety); five questions to assess the five subscales of the Difficulties in Emotion Regulation Scale (DERS [60,61]), which are emotional lack of control, emotional rejection, life interference, lack of emotional attention, and emotional confusion (e.g., “During this day, to what extent have you paid attention to your feelings?”); two questions that refer to the two subscales of the Emotion Regulation Questionnaire (ERQ [66,67]), which are reappraisal and suppression (e.g.,” During this day, to what extent have you been able to control your emotions by changing the way you think about the situation you were in?”); two questions that refer to the two subscales of the Philadelphia Mindfulness Scale (PHLMS [64,65]), which are acceptance and awareness (e.g., “During this day, when your emotions have changed, to what extent have you been aware of it immediately?”); one question to assess experiential avoidance based on the Brief Experiential Avoidance Questionnaire (BEAQ [62,63]) (“During this day, would you say that one of your biggest goals has been to be free of any painful emotion?”); one question from the Emotional Eating Scale (EES [72]) regarding the impulse to eat as a consequence of having experienced an intense emotion (“During this day, to what extent have you felt the urge to eat as a result of experiencing intense emotions?”) and one last question from the Body Satisfaction Questionnaire (BSQ [70,71]), which asks about the extent to which the participant has been satisfied with their body image (“During this day, how satisfied have you been with your body image?”).

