#### 2.5.4. Assessment during Treatment

The assessment during treatment battery involves continuing to fill in the same baseline questions once a week. In addition, before starting each online session, participants will be asked to fill in an emotional scale to assess its presence, intensity, and interference during the last week. Participants can choose the emotion or emotions that should be assessed. The UP offers four different emotional rating scales: The Overall Anxiety and Depression Severity and Impairment Scales (OASIS; ODSIS [74,75,76]), Other Emotions Severity and Impairment Scale (e.g., guilt, shame, or anger) (OESIS [77]), and a Positive Emotion Severity and Impairment Scale (e.g., happiness) (PESIS [77]; Supplementary Materials). All of them are used in the UP to help patients to continuously monitor the scores throughout the sessions and their progress over the treatment.

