Another aspect that we consider important to analyze is how the participants change their scores in each of the variables evaluated based on the content addressed each module. For this purpose, a visual analysis of the changes in the scores will be carried out, to see how the slopes change in the different phases of the study (evaluation and treatment), and in the different modules within the treatment. This visual analysis has been used in previous studies [21]. To carry out this visual analysis, the data from 19 questions that the participants will fill in weekly will be used.

Attendance at sessions will also be recorded to calculate the attendance rate, which will be used as an indicator of viability and acceptance of treatment by users. For the same purpose, quantitative and qualitative analyses will be carried out. At the quantitative level, the participants’ evaluation of and satisfaction with the treatment received will be evaluated using an ad hoc designed questionnaire (see “Measures” section). Qualitatively, participants will be asked to answer six main questions about treatment, and their answers will be analyzed by selecting and classifying the information through a segmentation process, identifying key themes and categories of analysis [80].

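### Module-by-module slopes cannot be read from one or two weekly points per module; the slope comparison these data support is baseline against the whole treatment phase

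*Protocol article*

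**What the plan says.** Section 2.6 of the protocol article sets out a visual analysis of score changes "to see how the slopes change in the different phases of the study (evaluation and treatment), and in the different modules within the treatment". It describes the input this way: "the data from 19 questions that the participants will fill in weekly will be used".

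The sampling schedule is given elsewhere:

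- **Baseline (2.5.3).** The battery is daily: "To facilitate the daily baseline assessment, we have summarized in one item the variable we want to evaluate". The example items ask about the current day.
- **Treatment (2.5.4).** The battery means "continuing to fill in the same baseline questions once a week".
- **Stagger (section 2).** "each patient will be randomly assigned to one of the multiple baseline conditions: 8, 12, or 15 evaluation days before the intervention". Under 2.2, session 1 is individual and is given when a participant's own baseline ends; the later sessions are in groups. There are twelve weekly sessions.
- **Density standard (section 2).** The baseline lengths are justified by the standard of "having a minimum of five data points in each phase".
- **Battery size.** In 2.2 the instrument used at baseline and during treatment is "an online survey made up of 14 questions". In 2.5.3, "participants will answer a battery of 19 questions".

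**The concern.** A slope needs at least two points, and needs more than two before it can be told apart from day-to-day variation. At one report a week, modules of one or two sessions cannot supply them. No later analysis plan can repair this, because the schedule does not collect the data. The OASIS, ODSIS, OESIS and PESIS do not fill the gap: Table 3 shows them in treatment only, also once per session, with no baseline values.

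Two related features affect how the same plots are read. Sampling frequency changes exactly where the phases meet, while 2.6 describes the data only as weekly. And the baselines differ by a week or less, so weekly treatment reports add little to the staggered comparison.

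What is at stake is interpretation. Single-item fluctuations between two adjacent weeks could be reported as the effect of a particular module, and a change in plotting density could be mistaken for a change in trend.

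**Working it through.** This is counting; alpha, power and effect size play no part. Assumptions: one battery per session week and no missed reports.

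**1. The article's own standard, by phase.** Section 2.6 names the phases as evaluation and treatment, with modules lying inside treatment.

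- Baseline: 8, 12 or 15 daily points; with one missed day, 7, 11 or 14.
- Treatment: 12 sessions × 1 report per week = 12 points.

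All are at least 5, so the per-phase minimum is met as written.

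**2. Points per module.** Sessions are grouped by their Table 2 titles. For a straight line, residual degrees of freedom = points − 2.

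| Module (short label) | Sessions | Points | Residual df |
|---|---|---|---|
| Goals and motivation | 1 | 1 | no slope |
| Understanding emotions | 2–3 | 2 | 0 |
| Mindful awareness | 4–5 | 2 | 0 |
| Cognitive flexibility | 6–7 | 2 | 0 |
| Emotional behaviors | 8 | 1 | no slope |
| Physical sensations | 9 | 1 | no slope |
| Exposures | 10–11 | 2 | 0 |
| Accomplishments and future | 12 | 1 | no slope |

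The total is 1+2+2+2+1+1+2+1 = 12. Four modules have no slope, and four have a line through two points.

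**3. Treated points inside the stagger.** Suppose two participants start baseline on the same day and session 1 comes the day after baseline ends. With baselines of a and b days (a < b), the window runs from day a+1 to day b and has b − a days. If the first weekly report comes o days after session 1, reports fall on days a+1+o, a+8+o, and so on. The offset o was run from 0 to 7.

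| Pair | Window (days) | Weekly treated points | If reports stayed daily |
|---|---|---|---|
| 8 vs 12 | 12 − 8 = 4 | 1 for o = 0–3, otherwise 0 | 4 |
| 12 vs 15 | 15 − 12 = 3 | 1 for o = 0–2, otherwise 0 | 3 |
| 8 vs 15 | 15 − 8 = 7 | 1 for o = 0–6, 0 for o = 7 | 7 |

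The maximum is one in every pair. A delay before session 1 could change these counts.

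**4. The time axis.** Let the score drift by a constant β per day with no treatment effect. Plotted by assessment number, the step is β in baseline and 7β in treatment, a ratio of 7. Plotted by calendar day, it is β in both.

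**5. Item count.** The items listed in 2.5.3 are 6 (emotions) + 5 (DERS) + 2 (ERQ) + 2 (PHLMS) + 1 (BEAQ) + 1 (EES) + 1 (BSQ) = 18. The same section and 2.6 say 19; 2.2 says 14.

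**The case against.** The strongest reply is that the analysis is visual. Section 2.6 specifies no fitted line or test per module, and 2.2 states the aim as watching how participants evolve across modules. A 12-point trajectory marked by module can be drawn and inspected. That stands, and it is why descriptive module displays are worth keeping. It does not rescue the word slopes: a one-point module has none, even by eye.

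Three stronger readings are tempting, and the article does not support them.

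- **That the plan breaks its own five-point minimum.** That minimum is stated per phase, and both named phases meet it. Modules and stagger windows are not called phases.
- **That the stagger is almost unobserved.** The counts in step 3 require a common baseline start. The article does not state one: patients are enrolled consecutively and recruitment runs from September 2020 to December 2024. The hypotheses and expected results rest on the RCI and on group comparisons between time points; no analysis described relies on concurrent contrasts within these windows.
- **That a seven-fold artefact is built in.** It arises only on an assessment-number axis. The article names no axis, and a condensed article may leave that to the full protocol.

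It is also fair to say that the item-count mismatch is a separate reporting matter and lends no weight to the slope argument.

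**Conclusion.** The point holds in a limited form. The per-module slope reading announced in 2.6 cannot be delivered for any of the eight modules at the planned weekly frequency. This rests only on the weekly schedule and Table 2; missed reports would lower the counts further. The phase-level comparison, 8 to 15 daily points against about 12 weekly points, remains possible provided the time scale respects the change in frequency.

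The stagger result, at most one weekly treated point while a later condition is still in baseline, is conditional on aligned baseline starts and an immediate session 1. On those terms the staggered comparison gains little from the treatment-phase data.

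The battery inconsistency (14, 19 and a listed 18), and the description of the data as weekly when baseline is daily, are real but secondary. The pre-treatment, post-treatment and follow-up comparisons are unaffected. The change should be made, but it concerns a supporting analysis.

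**What to change.** Wording changes, at almost no cost:

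1. In 2.6, remove the claim about slopes within modules. Show scores annotated by module, or module means, and label them descriptive.
2. Base the visual slope comparison on baseline against the whole treatment phase, with calendar days on the time axis.
3. State in 2.6 that baseline data are daily and treatment data weekly.
4. Settle on one item list and one count, and use it in 2.2, 2.5.3 and 2.6.

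Optional, with some participant burden: continue the daily battery for two weeks after session 1. Under the same alignment assumptions this gives 4, 3 and 7 treated points in the 8-vs-12, 12-vs-15 and 8-vs-15 windows. Only the last reaches five, so it improves the stagger without fully repairing it.
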